### Target population

The target population is patients with bipolar 1 or 2 affective disorder at increased risk of further relapse (an episode in the last 24 months). In clinical practice patients at increased risk of further relapse are the targets for interventions aimed at preventing further relapse rather than patients who have been stable for several years.

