### Inclusion/exclusion criteria

Inclusion criteria are:

• a SCID-DSM-IV verified diagnosis of primary bipolar disorder [22],

• at increased risk of relapse (at least one episode in the last 24 months),

• age 18 years or more.

Exclusion criteria are:

• presence of a current manic, hypomanic, mixed affective or major depressive episode currently or within the previous four weeks,

• current suicide plans or high suicide intent,

• inability or unwillingness to give written informed consent to the study.

• inability to communicate in written and verbal English to a sufficient level to allow them to complete the measures and take part in the groups.

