### Sample size

When patients receive treatment in groups, interactions between patients may lead to correlation of outcomes of patients in the same group [52] sometimes referred to as cluster. As with cluster randomised trials, sample size calculation needs to consider the possibility of intra-cluster correlation [53]. As there are no previous trials of group interventions for bipolar disorder that have considered clustering, we considered empirical evidence regarding the magnitude of clustering from cluster randomised trials. A previous trial [54] found a negligible clustering effect (0.0001) but this was from a small sample, and so would be imprecisely estimated. We have therefore assumed a small but not zero clustering effect equal to 0.05. Based on the outcomes from the two previous Barcelona protocol psychoeducation randomised controlled trials [7,8] a differential treatment effect of 0.22 was used (60% recurrence in the control group, 38% in the psychoeducation group). Power for 80% probability of detecting a difference at 0.05 level, 2-tailed testing requires 82 patients per arm. Assuming a mean group size of 18 and an intra-cluster correlation coefficient of 0.05, a design effect of 1.85 gives a sample size of 152 in each arm. We have assumed 15% loss to follow up [54] giving a total sample size of 179 per arm (358 in total). This is achieved by running 10 groups of 18 subjects in each arm (10 in the North West and 10 in the East Midlands) over 3 years. Initially 17-18 patents are recruited per group but with attrition there will be 13-14 patients per group, the ideal size for group psychoeducation based on 10 years experience [55].

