### Analysis

Intention to treat using Kaplan-Meier recurrence-free curves with significance tests will be based on the Cox proportional hazards regression model. The level of dependence or heterogeneity among patterns of recurrence

within the same team was estimated by the intracluster correlation coefficient (ICC) using estimate of frailty from the shared frailty model [60]. Trial centre, and number of previous episodes of bipolar disorder, will be included as covariates. Analysis of quantitative secondary outcome measures will use linear mixed models including baseline covariates and random effects for therapy group [52]. The treatment effect may differ according to illness duration/number of episodes with a lesser treatment effect in patients with longer illness duration/more episodes based on findings of the MRC CBT trial [21]. This will be tested in a secondary analysis by adding a severity-treatment interaction into the above models.

The economic analysis will be adjusted for baseline covariates shown to be important predictors of future costs and outcomes (e.g. costs and service use prior to entry, health status and utility, clinical severity and duration of illness, socio-economic status). Bootstrap simulations will be used to estimate cost effectiveness acceptability, net benefit statistics and the likelihood that group psycho-education is cost effective compared to group support. Probabilistic simulation models will be used to explore the generalisability of the results to the UK.

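### Time since the last episode decides who enters the trial but is not among the stated covariates of the primary Cox model, so a modest precision gain is forgone

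*Protocol article*

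**What the plan says.** The Target population section describes "patients with bipolar 1 or 2 affective disorder at increased risk of further relapse (an episode in the last 24 months"), and contrasts them with people who have been well for several years. The inclusion criteria repeat the threshold: "at increased risk of relapse (at least one episode in the last 24 months"). The exclusion criteria set the near end of the window by ruling out anyone with a manic, hypomanic, mixed or "major depressive episode currently or within the previous four weeks". Time since the last episode at entry therefore runs from about 1 to 24 months.

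Allocation is by minimisation on clinical site and on number of previous episodes in three bands (Design; Randomisation and treatment allocation). For the primary analysis, the Analysis section says: "Trial centre, and number of previous episodes of bipolar disorder, will be included as covariates". No other covariate is named for that model.

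Number of previous episodes is the one prognostic factor for which the protocol gives a size: relapse up to threefold higher in the highest band than in the lowest (Design). That factor is used in both the allocation and the model.

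**The concern.** Recency is the risk marker on which patients are selected. If risk falls with time since the last episode, it may well keep falling inside the 24 months and not only beyond them. Yet two patients with the same number of lifetime episodes, one five weeks and one 23 months from the last, look identical to both the allocation and the stated model. A lifetime count in bands captures current episode rate only in part.

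Two things are at stake. Adjusting a Cox model for a prognostic baseline variable usually gains some power, and here that gain is left unused. If the arms differed by chance in recency, the primary estimate would not be corrected for it.

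**Working it through.** **1. The planned sample size.** Two inputs come from the Sample size section. The assumed rates are "60% recurrence in the control group, 38% in the psychoeducation group". The stated requirement before any allowance for clustering or loss is "Power for 80% probability of detecting a difference at 0.05 level, 2-tailed testing requires 82 patients per arm".

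- Two-proportion formula, pooled variance under the null, mean rate 0.49: n = [1.96 × √(2 × 0.49 × 0.51) + 0.842 × √(0.60 × 0.40 + 0.38 × 0.62)]² / 0.22² = 79.9, so 80 per arm. This is within two patients of the stated 82.
- "Assuming a mean group size of 18 and an intra-cluster correlation coefficient of 0.05, a design effect of 1.85": 1 + (18 − 1) × 0.05 = 1.85, and 82 × 1.85 = 151.7, so 152.
- 15% loss: 152 / 0.85 = 178.8, so 179, matching "giving a total sample size of 179 per arm (358 in total").

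The figures reproduce. They rest on marginal recurrence rates with no covariate, so any mix of recent and remote patients is already inside the 60% and 38%. At an effective 82 per arm the two-proportion power is 81.0%.

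**2. What adjusting for recency would add.** I simulated Cox analyses with an effective 82 per arm (152 / 1.85, clustering not modelled explicitly), exponential times censored at the end of follow-up, control recurrence fixed at 60%, and a conditional hazard ratio of ln(0.62) / ln(0.40) = 0.522. Recency was uniform over the window. R is the assumed hazard ratio between its most recent and most remote ends. There were 4,000 trials per R.

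| R (assumed) | Power without recency | Power with recency | HR without | HR with |
|---|---|---|---|---|
| 1 | 81.5% | 81.4% | 0.522 | 0.521 |
| 1.5 | 82.5% | 82.7% | 0.521 | 0.518 |
| 2 | 81.1% | 81.7% | 0.524 | 0.518 |
| 3 | 80.8% | 83.0% | 0.526 | 0.515 |
| 5 | 77.6% | 82.5% | 0.542 | 0.519 |

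The simulation error of one power figure is about √(0.8 × 0.2 / 4000) = 0.6 points. The two models were fitted to the same data, so comparisons should be made within a row. Under no treatment effect (2,000 trials per R), the model without recency rejected in 4.2% to 5.7%. That is nominal, given a simulation error of about 0.5 points.

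The 77.6% at R = 5 is not a shortfall against the plan. The conditional hazard ratio was held at 0.522, so recurrence in the treated arm rose to 39.4%, and the true difference was smaller than the planned 22 points.

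**3. Cross-check on another scale.** A second simulation used 358 patients, clustering ignored, half recent and half remote, 400 trials per setting. When recent patients relapse at 1.5, 2 or 3 times the rate of remote ones, adjustment is worth about 2%, 8% or 19% more patients. The mean hazard ratios without and with adjustment were 0.521/0.516, 0.530/0.516 and 0.552/0.522.

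These look larger because a split into halves spreads risk more widely than a uniform gradient of the same ratio. Matching the standard deviation of the log hazard, ln(2)/2 = ln(R)/√12 gives R ≈ 3.3, and ln(3)/2 = ln(R)/√12 gives R ≈ 6.7. An 8% gain from 80% power gives 2.80 × √1.08 = 2.91, and 2.91 − 1.96 = 0.95, which is about 83% power. This agrees with the R = 3 row.

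**4. Chance imbalance.** For uniform recency over 23 months, SD = 23/√12 = 6.6 months. The standard error of the difference in means between arms of 179 is 6.64 × √(2/179) = 0.70 months. At R = 3 the log hazard changes by ln(3)/23 = 0.048 per month. An imbalance of one standard error would therefore move the hazard ratio by a factor of about exp(0.048 × 0.70) = 1.03, and one of two standard errors by about 1.07.

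**The case against.** The strongest reply is that nothing here is wrong. The 24 months are an entry threshold, set against several years of stability, and the protocol nowhere says that risk is graded inside it. It does adjust for the factor whose gradient it quantifies. A further prognostic covariate is something an analysis plan may add, and one may exist. All of this stands, and it is why the point is an improvement and not a fault. What remains is that the Analysis section names the covariates of the primary model and recency is not among them. An analysis plan that added it would settle the point.

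A reader might go further and infer that the trial loses power and that its treatment effect is diluted. The document does not support either. Planned power rests on marginal rates and assumes no adjustment, so nothing is taken from it. The hazard ratio moves slightly towards 1 without adjustment because the marginal and conditional hazard ratios are different quantities (non-collapsibility). A truly smaller benefit would need treatment to interact with recency, and the only modifier the protocol describes is illness duration or number of episodes.

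Two practical objections also stand. Eligibility can be settled by yes/no answers, so an exact end date may not be recorded. Randomisation waits until at least 20 participants in a wave are identified, so recency at the baseline interview may differ from recency at randomisation, where follow-up starts.

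**Conclusion.** The point holds as an optional efficiency improvement. The expected gain is about 0 to 2 points of power for an end-to-end gradient up to 3 and about 5 points at a gradient of 5, with essentially no loss if recency carries no information. The planned 80% power, type I error and validity are unaffected.

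The result rests on an assumed gradient, uniform recency, exponential times and an effective sample of 82 per arm. The simulations did not include number of previous episodes. Since that is already in the planned model, any prognostic information it shares with recency would make the real gain smaller.

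**What to change.** Before outcome data are seen, pre-specify time since the end of the last episode as an added covariate, next to trial centre and number of previous episodes, in the primary Cox model and in the models for time to next manic-type and time to next depressive episode. Take it from the baseline SCID and update it to the randomisation date. Use bands if exact dates are not recorded.

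The cost is a line of analysis wording and one recorded value: the episode end date has to be kept as a date or band and not only as an eligibility tick. Recall of it may be imprecise, which would reduce the gain. The allocation scheme need not change.

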### Ethics and research governance approval

The trial has received national multi centre research ethics approval (09/H0408/33) and research governance approval and permission at each participating health service delivery organisation. Each participant gives written informed consent to the trial and separately also gives written informed consent for the qualitative interviews. The trial is overseen by an independent Trial Steering Committee and Data Monitoring and Ethics committee organised by the research investigators for the purpose. The members of the committee are drawn externally from outside the institutions that the research team currently work to ensure its independence of the research team.

## Results

The study is now recruiting participants across the East Midlands and North West areas of England in the form of a rolling road show visiting centres sequentially.

## Discussion

Although there is evidence from two RCTs of the clinical efficacy of group psychoeducation for bipolar disorder compared to group support in a specialist bipolar disorder service in Spain [7,8] and clinical effectiveness versus treatment as usual in an Australian RCT [12], the evidence base is still relatively thin. In particular, evidence is still required about whether the content and style of group psychoeducation has any specific effect on time to relapse and other clinical and economic outcomes. From a United Kingdom service commissioning perspective, there is a need to establish that group psychoeducation is more clinically and cost effective than the support groups that are quite commonly found in the United Kingdom. These support groups are cheap to fund as they are largely run by charities using expert patients rather than trained professional therapists. Thus this study is designed primarily to establish whether it is the content and style of the intervention delivered in group psychoeducation that is more effective and cost effective than an active control intervention of the same length and duration of treatment, taken by therapists of the same professional background and with the same specific aim of trying to develop a plan of care to stay well over time. However, the study has been adapted to be a pragmatic randomised controlled trial of these interventions to reflect a model that might be used in everyday clinical practice in England. Thus unlike the Barcelona trials, there is an expert patient as a facilitator. In England it is increasingly common to use such patients in this role in England. There may also be advantages in terms of relating the therapists' interventions more closely to patient experience and also costs to health services [15,59]. Furthermore we have used a range of different health professionals to reflect clinical practice in England rather than only psychiatrists and clinical psychologists as in the Barcelona trials.

Seven features of trial design and conduct may distinguish a pragmatic RCT from an efficacy or more theoretically driven RCT [61]. On such a continuum, our current RCT has more features of a pragmatic RCT than an efficacy RCT but some compromises have been made so that it can achieve its primary objective, which is arguably primarily theoretical. Thus the study question has a theoretical component to it and as such the control intervention in terms of length and duration of treatment and professional background of the therapists does not reflect the reality of most expert patient groups providing support for bipolar disorder in United Kingdom. They are run by expert patients rather than professional therapists, are either closed and run for fewer sessions or open ended and open to new membership, and may have some content similar to that found in the group psychoeducation intervention.

On the other hand a pragmatic RCT design approach has been taken in terms of other features of the study design. Broad inclusion/exclusion criteria of the group participants have been applied with exclusions applying only to lack of clarity around diagnosis or an inability to participate in the intervention as would be required in routine clinical practice, where access to interventions and generalisability of findings are a primary concern. Hence the setting is not a specialist bipolar disorder service with highly trained therapists [7,8], but routine health services using therapists with limited experience of the specific interventions, but with clinical or personal experience of bipolar disorder and often previous experience of delivering psychological interventions. The group psychoeducation intervention has been adapted from the content of the published manual [55], both to keep it up to date with a fast changing field of evidence based practice but also on the advice of a panel of service users and health professionals, some changes to the content of some of the sessions and the materials or scenarios used to fit well with an English clinical setting. For instance, the first session might not engage English patients if it did not directly tackle the nature of bipolar disorder and was restricted to introductions and rules about running the group. There is also a greater emphasis on the family, less need to tackle ideas from established religion, a need to consider English service structures e.g. crisis resolution and home treatment teams and community mental health teams [20], and how they could be utilised with a more extended early warning signs intervention.

The main strengths of the RCT are the size of the sample and its multi-site design allowing consistency of intervention effects and their generalisability to be explored. Unlike a psychological treatment study compared against treatment as usual or a briefer intervention, it may be possible to achieve independent and blinded rating of outcome because both interventions are similar in form and duration but differing in content. Outcomes are assessed using well-validated measures that we have applied successfully before in a series of RCTs on psychological interventions in bipolar disorder. Furthermore although the trial has a clear theoretical aim, it is carried out using methods that are relatively close to usual clinical practice settings, again allowing the results to be readily generalisable to routine clinical practice. The combination of qualitative and quantitative data collection around mechanisms of action, the nature of the intervention and its effects, and barriers to its delivery allows sufficient detail both to replicate these complex interventions and optimise their delivery for both further research and clinical practice [62].

The main weakness of the current RCT is the lack of a treatment as usual group. Whilst the trial will report on the relative clinical and cost effectiveness of the two interventions it cannot definitively show that either is more clinical or cost effective than treatment as usual. The process measures will be able to track whether key processes are changing in the groups, particularly in the group psychoeducation intervention. Thus, in both groups there should be evidence of group cohesion if these interventions are likely to be effective but in addition the specific content of the group psychoeducation intervention should show improvements in knowledge about bipolar disorder, early warning signs and adaptive strategies, and regularity of social rhythm coping. If such changes are not happening over time in the participants who have adhered to the group psychoeducation, then it is less likely that group psychoeducation had been effective in this RCT. While group psychoeducation has demonstrated improvements in medication adherence [63], previous psychological treatment studies performed by our group [21,51] have not demonstrated such benefits because of ceiling effects with high levels of medication adherence in both intervention and treatment as usual groups.

Other potential weaknesses include uncertainty concerning the design effect of the study due to clustering and potential difficulties in recruitment because the onset of the study is delayed until sufficient size groups are recruited. Both these factors may adversely affect the sample size needed to show a true difference in effectiveness between the two treatment groups. The relative inexperience of the therapists may also dilute the effectiveness of both treatments although they may reflect a more accurate picture of their effectiveness in routine clinical practice settings.

In terms of research implications, the trial will provide a rigorous test of whether the content and style of group psychoeducation similar to that provided in the trials from Barcelona is effective. If so the trial will produce more evidence concerning its mode of action. From a clinical implementation perspective, the cost effectiveness of the interventions and barriers and drivers to the delivery of the intervention will enable service providers to decide whether the intervention is worth providing and also how best to deliver it.
